### Outcomes

#### Primary outcome measure

Our primary outcome measure is difference between the two treatment groups in long-term control as measured by POEM scores captured weekly over the first 16 weeks. POEM is a patient-reported outcome based on symptoms over the previous week which can be completed by the child's carer or the child themselves.^24^ POEM is the only patient-reported outcome that demonstrated sufficient validity and repeatability in a systematic review of outcome measures for eczema^25^ and has been recommended as the preferred instrument for capturing patient-reported symptoms in eczema trials by the Harmonizing Outcome Measures for Eczema initiative (http://www.homeforeczema.org). Our primary outcome measure is based on repeated measures of POEM data collected weekly over 16 weeks because this reflects the impact of this relapsing and remitting chronic condition better than comparing outcomes at a single follow-up point. However, if weekly questionnaires prove too burdensome for participants and there is excessive missing data, we will consider change in POEM score from baseline to 4 months as our primary outcome.

Because of the burden of weekly questionnaires on participants, we have limited weekly data collection to the first 16 weeks of the trial for the primary outcome assessment but follow-up will continue for 12 months. Participants may choose to complete questionnaires either online or by post. See table 1 for schedule of observations.

**Table 1 BMJOPEN2015009575TB1:** Schedule of observations

Outcomes collected	Prescreen	Baseline	Weekly for 15 weeks	16 weeks	4 weekly for 32 weeks	52 weeks
Carer-reported outcomes						
UK diagnostic criteria for eczema	✓	✓				
Eczema severity over past year (NESS)	✓					
Demographics		✓				
Prior belief in bath emollients	✓	✓		✓		✓
Service use		✓		✓	✓	✓
Medication use		✓		✓	✓	✓
Eczema severity over past week (POEM)		✓	✓	✓	✓	✓
Eczema-related quality of life (DFI)		✓		✓		✓
Generic quality of life (CHU-9D)		✓		✓		✓
Questions about washing		✓		✓		✓
Adverse effects from bathing		✓	✓	✓	✓	✓
Adherence/avoidance of bath emollients	✓	✓		✓		✓
Review of GP records for 12 months from recruitment						
Number of consultations*						✓
Referrals for eczema						✓
Medication use						✓

*Consultations will be categorised into the following four groups:

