#### Secondary outcome measures

Secondary outcomes include differences between groups in POEM scores captured monthly over 12 months.

We will analyse differences between groups in number of eczema exacerbations resulting in a primary healthcare consultation over 12 months measured by GP notes review. Exacerbations will be defined as consultations where there is mention of eczema and topical steroid or topical calcineurin inhibitor has been advised or prescribed (see table 1 schedule of observations for further detail). We will also measure dermatology referrals and prescribing for eczema over 12 months by GP notes review. We will assess service use and medication use by carer report, in addition to GP notes review.

We will ask both groups about use of bath emollient in order to assess adherence to treatment allocation. Adverse effects of bathing, such as stinging in the bath or slipping in the bath or bathroom will also be asked in both groups to allow exploration of any differences between groups.

Differences between groups in change from baseline in disease-specific quality of life at 4 and 12 months will be measured by Dermatitis Family Impact (DFI). DFI^26^ is a widely used validated instrument measuring impact of eczema on the family's quality of life.

We will measure differences between groups in change from baseline in generic quality of life at 4 and 12 months, using the Child Health Utility 9D (CHU-9D).^27^ The use of EQ-5D in children has been questioned and it does not capture quality of life issues pertinent to childhood eczema. The CHU-9D is a paediatric generic preference-based utility measure exclusively developed with children aged 7–11 years and is more suitable for capturing quality of life impact related to eczema, such as sleep disturbance and child's mood. Personal communication with the team who developed this measure confirmed that studies are underway trialling its application in children aged 5–7 years but, to our knowledge, there are no studies reporting for infants. There are no suitable utility measures validated for very young children aged 1–4 years, but the CHU-9D performed well in a similar population in the SPaCE feasibility trial (CHU-9D data currently being prepared for publication).^28^

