### Sample size

The sample size was calculated for repeated measures analysis of covariance (ANCOVA) in weekly POEM scores over 16 weeks. Using data from a similar population in the SWET trial,^30^ we aim to detect a mean difference of 2.0 (SD 7.0) between intervention and control groups. An α of 0.05 and power 0.9 gives a sample size of 338. Allowing for 20% loss to follow-up, this gives a total sample size of 423 children.

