### Statistical methods

We will use repeated measures ANCOVA to explore whether there is a significant difference between mean POEM scores over the 16-week period in the intervention and standard care groups. The analysis will control for possible confounding effects of key covariates, such as baseline eczema severity and age of child. However, because ANCOVA relies on analysis of complete cases only, the levels of missing data will be reviewed and, if appropriate, the data will be analysed using mixed models instead, which allows incomplete cases to contribute to the analysis. There will be no interim analyses.

For the analysis of secondary outcomes, repeated measures analysis in line with that used for the primary outcome will be used for the monthly POEM measure up to 1 year. For other secondary outcomes, linear regression will be used for continuous outcomes if the assumptions are met. Otherwise non-parametric analyses will be used. Logistic regression will be used for dichotomous outcomes and a suitable count model, as determined by goodness of fit measures, for count data. All analyses will control for potential confounders.

Primary analyses will be carried out on an intention to treat basis, according to the CONSORT definition^31^ whereby all participants are included in the group to which they were assigned, whether or not they completed the intervention given to the group. We will consider carrying out a per protocol analysis in addition to this if monitoring reveals a substantial proportion are not following their treatment allocation (ie, intervention group stop using bath emollient or control group start bath emollient). We will carry out a sensitivity analysis based on prior belief in bath emollients, to explore whether this appears to have any influence on outcomes. The statistical methods will be finalised in a statistical analysis plan, which will be made available on the study website.

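### DFI and CHU-9D are measured at both 16 and 52 weeks but assigned to linear regression; without imputation, the 12-month comparison ignores the week-16 scores of children lost later, costing a little precision and risking bias if dropout differs by arm

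*Protocol article*

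**What the plan says.** Under Secondary outcome measures, the article defines the DFI comparison as "Differences between groups in change from baseline in disease-specific quality of life at 4 and 12 months", and for CHU-9D says "We will measure differences between groups in change from baseline in generic quality of life at 4 and 12 months". Table 1 places both instruments at baseline, 16 weeks and 52 weeks, so each child can contribute two follow-up scores per scale.

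Statistical methods gives the primary outcome a repeated measures ANCOVA. It sees a weakness there, "because ANCOVA relies on analysis of complete cases only", and offers a way out: "if appropriate, the data will be analysed using mixed models instead, which allows incomplete cases to contribute to the analysis". The same approach is carried over to monthly POEM up to one year. Everything else continuous gets one sentence: "For other secondary outcomes, linear regression will be used for continuous outcomes if the assumptions are met", with non-parametric analysis as the fallback. The section adds that all analyses adjust for potential confounders, names baseline eczema severity and age as key covariates, and leaves final methods to a statistical analysis plan. It does not say how missing secondary outcomes will be handled.

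**The concern.** Read as written, DFI and CHU-9D get a separate regression at each time point. A child who returned the week-16 form but not the week-52 form then contributes nothing to the 12-month estimate, although the observed week-16 score is the best available guide to the missing value. The section identifies this weakness and names a remedy for POEM, but does not extend it to the other two repeated scales.

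Such children are likely to exist. Under Data collection methods, the gift voucher is tied to the 16-week questionnaire, which is also the example given for telephone reminders; the 52-week questionnaire earns entry to a prize draw.

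Dropout that differs by arm is also conceivable. The trial is open-label, and in the pretrial survey (Table 2) 117 + 30 = 147 of 207 carers (71%) used bath emollients all or almost all of the time. That sample was recruited online through eczema organisations, so it is only indicative. Still, standard-care families whose child was doing badly at week 16 might leave for reasons that do not apply in the other arm. At stake are the precision and possibly the validity of the 12-month quality-of-life effects.

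**Working it through.** **The plan's own figure.** The article gives no sample size, SD or target difference for DFI or CHU-9D. The only loss figure is under Sample size: "Allowing for 20% loss to follow-up", the 338 children become 338/0.8 = 422.5, that is 423, as stated. This 20% belongs to the 16-week POEM calculation. No 12-month figure is given, so 20% is used below as an assumption.

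**Assumed inputs (not in the article).** Correlations: baseline–week 16, 0.5; baseline–week 52, 0.4; week 16–week 52, 0.6. Scores are in SD units, higher meaning worse. Both analyses adjust for the baseline score. Loss is 20%, after week 16 unless stated.

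**Precision.** The partial correlation of the two follow-up scores given baseline is

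(0.6 − 0.5 × 0.4) / √[(1 − 0.5²)(1 − 0.4²)] = 0.4 / √(0.75 × 0.84) = 0.504, squared 0.254.

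With random loss, the variance of the joint-model effect relative to regression is 1 − 0.2 × 0.254 = 0.949, a saving of about 5%. Simulated trials with 423 children gave ratios of 0.951 to 0.963. The saving is therefore about 4–5%.

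**Bias.** Regression at week 52 in children with a 52-week score was compared with a likelihood estimate that also uses week 16. Slopes are log-odds of dropout per SD of worse week-16 score, standard care v bath emollient.

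| Dropout pattern | Regression bias (SD) | Joint-model bias (SD) |
|---|---|---|
| Random | 0.00 | 0.00 |
| Depends on baseline severity | 0.00 | 0.00 |
| Same slope in both arms | 0.00 to 0.02 | 0.00 |
| 0.3 v 0 | about 0.02 | 0.00 |
| 1.2 v 0.8 | about 0.02 | 0.00 |
| 0.8 v 0.4 | about 0.03 | 0.00 |
| 0.8 v 0 | about 0.06 | 0.00 |
| 1.2 v 0 | about 0.08 | 0.00 |

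The upper end of the same-slope row arises with a real effect: on an SD of 7, a true −2.00 is estimated as −1.89, and 0.11/7 = 0.016 SD. Where worse scores drive loss mainly from standard care, the remaining controls look better than the full arm, so a benefit of bath emollient is understated. If the slopes run in opposite directions (about 1.05 v −1.05), the bias is 1.03/7 = 0.15 SD, but that pattern is extreme.

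**Scale.** With 338 children observed at week 52, the standard error of the adjusted effect is about √(4 × 0.84/338) = 0.10 SD. A bias of 0.02–0.08 SD is therefore about 0.2 to 0.8 of a standard error.

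**Limits of the remedy (slopes 0.8 v 0).** If half the loss occurs before week 16, bias falls only from about 0.06 to about 0.03 SD. If all of it does, both methods give about 0.06. If dropout follows the week-52 state itself, bias is about 0.13 with regression and 0.09 with the joint model.

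**The case against.** The strongest reply is that the article names a model family and nothing more. Linear regression is compatible with multiple imputation that uses the week-16 score, the section defers to a statistical analysis plan, and its complete-case remark concerns the primary ANCOVA. A reader might infer that the trial has committed itself to a complete-case 12-month analysis; the article does not say so. This stands, and it is why the point is conditional on no imputation. It does not remove the point: the choice of regression for two repeated scales is stated, beside a better method that the section already names.

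Three further inferences are tempting and unsupported:

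- That any dropout related to eczema biases the comparison. Dropout that follows baseline severity is handled by baseline adjustment, and a common rule in both arms leaves almost no bias.
- That the bias is a large share of the effect the trial is designed to find. The design difference of 2.0 with SD 7.0 (0.29 SD) is for POEM. None is stated for DFI or CHU-9D, and the larger biases need a strong dropout slope in one arm and none in the other.
- That the cost-utility analysis is distorted. Health economic analysis says CHU-9D supplies the utilities, not that this regression feeds that analysis.

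It is also fair to say that baseline-adjusted regression at each time point is conventional and that the precision gain is small.

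**Conclusion.** The point holds as an improvement to a stated method, not as an error that invalidates a result. Without imputation, the 12-month DFI and CHU-9D comparisons discard usable week-16 data, at a cost of about 4–5% of variance. The effect may be biased by about 0.02–0.08 SD if dropout depends on post-baseline eczema differently by arm; otherwise bias is negligible. These sizes rest on one assumed set of correlations, an assumed 20% loss after week 16 and assumed dropout slopes. The article neither supports nor rules out differential dropout. In these scenarios the joint model was never worse than regression. The primary outcome and monthly POEM are unaffected.

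**What to change.** In Statistical methods, or in the statistical analysis plan to which it defers, extend the mixed-model approach named for POEM to DFI and CHU-9D. Fit one model per scale with the week-16 and week-52 scores as repeated outcomes, the baseline score and the primary-analysis covariates, a treatment-by-time term and an unstructured covariance. Report the 4-month and 12-month effects from it. With the baseline score as a covariate, the treatment effect on the score equals the effect on change from baseline, so the outcome definition is kept. Where the non-parametric fallback applies, use multiple imputation that includes the week-16 score. Keep linear regression for continuous outcomes measured once.

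This takes one or two sentences and no new data, visits or participants. The price is reliance on a missing-at-random assumption, though a weaker one than baseline-adjusted complete-case regression needs. Correction is only partial when children are lost before week 16.

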### Health economic analysis

The within trial economic analysis will include the primary economic evaluation which will be in the form of cost-effectiveness analysis. A secondary economic evaluation in the form of cost-utility analysis will be conducted using utility values obtained from the CHU-9D preference-based quality of life measure. Although the CHU-9D was not designed for use in very young children, it has been used among children aged less than 5 ([name], personal communication). All cost-effectiveness results will be presented on: (1) the cost-effectiveness plane, which captures the uncertainty around the results and shows the incremental cost and incremental effect of the comparison of interest in a two-dimentional plot, and (2) cost-effectiveness acceptability curves, which graphically represent the uncertainty, in terms of probabilities, regarding the cost-effectiveness of the new technology compared with the existing alternative. The cost-effectiveness unit of analysis will be: (1) the cost per unit change as measured by the primary outcome (POEM) at 16 weeks; (2) cost per exacerbation avoided over 1 year. If the latter is not possible then cost per unit score change of POEM measure at 1 year will be reported.

### Monitoring

The Trial Management Group is responsible for overseeing progress of the trial. An independent Trial Steering Committee will include Data Monitoring Committee roles because the trial is investigating bath emollients, used within their licensed range of indication, that are available without prescription and have been used for many years with no safety concerns. The Trial Steering Committee includes independent experienced triallist, medical statistician, dermatologist, and patient and public representative, following a standard National Institute for Health Research Health Technology Assessment (NIHR HTA) charter. No interim analyses are planned.

Information about expected adverse reactions to bath emollients which are listed in the Summary of Product Characteristics (ie, pruritus, reddening, itching, skin irritation, rash, accidental ingestion, slipping) will be collected in trial questionnaires (or withdrawal form, where applicable) and therefore need not be reported as an adverse event. Any unexpected adverse event which could reasonably have been caused by bath emollients will be reported.

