In addition to concerns about cost-effectiveness, potential harms from using bath emollients include skin irritation and greasier bath surfaces that can increase the risk of slips and accidents (listed in the Summary of Product Characteristics of leading brands). There is also a concern that people who use bath emollients in place of leave-on emollients are receiving substandard emollient therapy.^10^

The effectiveness of adding antiseptic agents to bath emollients has also not been demonstrated. Two small randomised studies^12^
^13^ compared ‘bath emollient’ with ‘bath emollient plus antiseptic’ on a range of outcomes, but there were no significant differences between groups, including colony counts of *Staphylococcus aureus*.^14^ For this reason, we chose to exclude bath emollients which incorporate an antiseptic, because of the absence of benefit and possible increased risk of skin irritation.^15^

Pragmatic clinical trials aim to test the effectiveness of an intervention in a real-life setting in order to recruit a study population that is as similar as possible to the population on which the intervention is meant to be used. Whereas an explanatory clinical trial aims to answer the question, ‘Can this intervention work under ideal conditions?’ a pragmatic approach seeks to answer the question, ‘Does this intervention work under usual conditions?’^16^
^17^ Features of pragmatic trials include: that they use clinically important outcomes, commonly participant-reported outcomes; that they include longer term follow-up; and that participants are encouraged to adhere to the intervention only to the extent that would be anticipated in usual care.

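### The adverse event exemption for slipping, accidental ingestion and other listed reactions rests on expectedness alone and sets no limit for serious cases

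*Protocol article*

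**What the plan says.** The Monitoring section of the protocol article names the expected reactions taken from the product information: "pruritus, reddening, itching, skin irritation, rash, accidental ingestion, slipping". Information on these "will be collected in trial questionnaires (or withdrawal form, where applicable) and therefore need not be reported as an adverse event". The sentence after it gives the reporting rule: "Any unexpected adverse event which could reasonably have been caused by bath emollients will be reported".

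On oversight, the same section says: "An independent Trial Steering Committee will include Data Monitoring Committee roles". Part of the reason given is that the products "have been used for many years with no safety concerns". No interim analyses are planned.

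Two other places bear on the point. The Background counts among the potential harms "skin irritation and greasier bath surfaces that can increase the risk of slips and accidents". The section on secondary outcome measures says: "Adverse effects of bathing, such as stinging in the bath or slipping in the bath or bathroom will also be asked in both groups". Table 1 schedules the item on adverse effects from bathing at baseline, weekly for 15 weeks, at 16 weeks, 4-weekly for 32 weeks, and at 52 weeks.

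**The concern.** Expectedness says whether a type of event is already known for the product. It does not say how bad a particular case is. Reddening or itching can sensibly be left to a routine form. Slipping and accidental ingestion are different: most cases will be trivial, but a few may not be, and the trial recruits children from just over 12 months of age. The rule treats all seven reactions alike.

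What is at stake is the speed with which a serious case is recognised and reviewed. A listed reaction is taken out of adverse event reporting because a questionnaire will pick it up. A questionnaire completed at intervals suits a comparison of frequencies at the end of the trial. It is not a means of bringing a single serious injury to the attention of the body responsible for safety while the trial is running.

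**Working it through.** The article gives no figure to reproduce on this point. The check is of the text, plus a count from Table 1.

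**Step 1: the two rules side by side (Monitoring).**

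| Event | Expected (listed)? | Under the exemption? | Under the reporting sentence? |
|---|---|---|---|
| Mild itching after a bath | Yes | Yes | No |
| Slip in the bath, no injury | Yes | Yes | No |
| Slip leading to hospital care | Yes | Yes | No |
| Accidental ingestion leading to hospital care | Yes | Yes | No |
| Unlisted event plausibly caused by the product | No | No | Yes |

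The second to fourth rows get the same treatment because neither sentence contains a seriousness criterion. The term serious adverse event does not appear in the article.

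**Step 2: against the Background.** The Background recognises slips and accidents as a possible harm of the products. Slipping is also on the exempt list. The two statements do not contradict each other, since Monitoring does arrange for slipping to be collected. But a harm that the authors foresee is removed from individual reporting whatever its consequence.

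**Step 3: timing of the substitute route (Table 1).** The post-baseline points are weeks 1 to 15 (15), week 16 (1), weeks 20 to 48 every 4 weeks (8) and week 52 (1): 15 + 1 + 8 + 1 = 25. The gap is 1 week up to week 16 and 4 weeks from week 16 to week 52. A carer's report may therefore fall due up to 4 weeks after the event, and later if a form is missed. The withdrawal form is the other named route, and it applies only to families who withdraw.

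**Step 4: from the forms to the committee.** The article does not say how, how quickly or whether answers on these items are passed to the Trial Steering Committee.

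**Step 5: scale, by assumption only.** The documents give no rate of serious events. With the planned total of 423, there are 423/2 = 211.5, say 211, children per arm. For an assumed yearly risk p, the chance of at least one event in an arm is 1 − (1 − p)^211:

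- p = 0.1%: 1 − 0.999^211 = about 19% (expected count 211 × 0.001 = 0.2)
- p = 0.5%: 1 − 0.995^211 = about 65% (expected count 1.1)
- p = 1%: 1 − 0.99^211 = about 88% (expected count 2.1)

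The range shows that the answer depends almost wholly on p. Nothing in the point rests on it.

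**The case against.** The strongest reply is that this is a condensed journal article. Definitions of serious events, forms, timelines and data flow usually sit in the full protocol, and the committee works under a standard charter that is not shown. A reader might infer that the trial deliberately leaves serious injuries unreported, or that they would reach the committee too late. The documents do not support either inference: they never say that serious cases are exempt, and the data flow is undescribed rather than shown to be slow. That part of the reply stands. It does not rescue the sentence, because the article does more than leave a detail out. It states an exemption, and the exemption has no limit.

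A reader might also infer that a carer questionnaire is the only record. That is too strong. The withdrawal form is named as well. Carer-reported service use, and the 12-month review of GP records with its residual category for consultations unrelated to skin, might also pick up an injury. None of these is described as a safety route, and Table 1 places the GP record review at 52 weeks.

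Nor is the comparison of harms lost, or limited to the intervention arm. Slipping is asked about in both groups at 25 post-baseline points, and return is supported by automated reminders, telephone reminders at key time points, a voucher and a prize draw. In an open trial, systematic questions put to both arms are a fairer basis for comparison than spontaneous reports. This part of the reply stands in full.

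**Conclusion.** The point holds in a limited form. As published, the exemption turns on expectedness alone and covers a slip or ingestion with serious consequences; the reporting sentence does not bring such a case back in. The article describes no prompt route for it to the Trial Steering Committee.

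The consequence is a possible delay in safety review of individual serious cases: up to 4 weeks before a form falls due after week 16, longer if it is not returned. There is no consequence for the primary analysis, and none for the planned questioning of both arms about adverse effects of bathing. How many cases would be affected is unknown. The probabilities above are conditional on assumed risks and should not be quoted singly.

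The conclusion assumes that the published sentences are the rule in force. If the full protocol has a separate procedure for serious events, the fault lies in the wording of the article and not in the conduct of the trial. The wording should be corrected in either case.

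**What to change.** In Monitoring, limit the exemption to non-serious occurrences of the listed reactions. Add that any listed reaction meeting the usual definition of serious is reported to the Trial Steering Committee, in either arm and whether or not it is expected. State the reporting route, or point to the section of the full protocol that gives it. If the full protocol already contains this rule, amend the published sentence to say so.

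The questionnaire items should stay as they are, since they supply the comparison between arms. The cost is about one sentence, a form for serious events if none exists, and a small number of extra reports. Sample size, visit schedule and analysis are unaffected.

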### Data management

Participants will enter their outcome data online into a validated database. Data will be stored on a secure server at the University of Southampton. Data collection from notes review and from participants who prefer to complete paper-based will be stored on paper in secure filing cabinets.

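### The exemption of expected bath emollient reactions from adverse event reporting is not limited to non-serious events, and no prompt route from the questionnaires to the oversight committee is stated

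*Protocol article*

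**What the plan says.** The Monitoring section of the protocol article sets a two-part rule.

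- **Listed expected reactions.** The list is "ie, pruritus, reddening, itching, skin irritation, rash, accidental ingestion, slipping". Information on these "will be collected in trial questionnaires (or withdrawal form, where applicable) and therefore need not be reported as an adverse event".
- **Everything else.** "Any unexpected adverse event which could reasonably have been caused by bath emollients will be reported".

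The same section gives the data monitoring role to the independent Trial Steering Committee. The reason offered is that the products are "used within their licensed range of indication, that are available without prescription and have been used for many years with no safety concerns".

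The Background names as a potential harm "greasier bath surfaces that can increase the risk of slips and accidents".

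Under Secondary outcome measures: "Adverse effects of bathing, such as stinging in the bath or slipping in the bath or bathroom will also be asked in both groups". In Table 1 the row "Adverse effects from bathing" is ticked at baseline, weekly for 15 weeks, at 16 weeks, 4-weekly for 32 weeks, and at 52 weeks. For online entries, Data management says: "Data will be stored on a secure server at the University of Southampton". Paper forms are kept in secure filing.

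**The concern.** A reporting rule normally has to separate events by seriousness as well as by expectedness. This one uses expectedness (and, for unlisted events, plausible causation). Two of the seven listed items, slipping and accidental ingestion, can range from trivial to serious, and the participants are children from just over 12 months of age. On the wording, a listed event that leads to hospital admission sits in the branch that need not be reported, while a minor unlisted event that the product might have caused sits in the branch that must be.

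What is at stake is timely review. The Background foresees slips and accidents, yet the article describes no step by which the serious form of that harm would promptly reach the committee responsible for safety oversight.

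**Working it through.** There is no figure in the plan to reproduce. The check is to apply the stated rule case by case and then follow where the information goes.

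**Step 1: apply the Monitoring rule.**

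- Listed and minor (for example transient itching): questionnaire or withdrawal form; no adverse event report. This is the evident purpose of the exemption.
- Listed and serious (for example admission after accidental ingestion): the same branch, because neither sentence mentions seriousness.
- Unlisted and plausibly caused by the product, of any seriousness: reported.
- Injury that follows a slip (for example a fracture): unclear. If the event is classed as the slip, it is exempt. If it is classed as the fracture, it is unlisted and reportable. The article does not say which.

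**Step 2: timing of the substitute channel (Table 1).**

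- To week 16: one form per week.
- After week 16: 4-weekly forms to week 16 + 32 = 48, then the week 52 form. The interval between forms is 4 weeks throughout.
- Duration of the sparser schedule: 52 − 16 = 36 weeks; 36/52 = 0.69, or 69% of follow-up.

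So a listed event may wait up to 1 week, and later up to 4 weeks, before a form that asks about it is due. A late or missing form lengthens that.

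**Step 3: look for a route from an answer to the oversight committee.**

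- Secondary outcome measures gives the purpose of the adverse-effect questions as exploring differences between the groups. Its examples are stinging and slipping; ingestion is not named there, although Monitoring says that the listed reactions are collected.
- Data collection methods describes automated reminders, with telephone reminders at key time points. It describes no screening of answers for seriousness.
- Data management describes storage only.
- Monitoring does not say which safety data the Trial Steering Committee receives, or when. It says that no interim analyses are planned.

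**Step 4: other channels that might pick up a serious event.**

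- Carer-reported service use (Table 1) is asked at baseline, 16 weeks, 4-weekly and 52 weeks, but not on the weekly forms. It may record a hospital visit; no link to the adverse-effect item is stated.
- The review of GP records covers 12 months and appears only in the 52-week column. Its four consultation categories turn on mention of eczema, rash, itch or dryness, so a consultation for an injury alone would fall in the last category.

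Both collect health service data. Neither is described as a safety-reporting route.

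**The case against.** The strongest reply has four parts.

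**The article is a condensation.** Definitions, timelines and sponsor reporting of serious events commonly sit in the full protocol. This stands: their absence here shows nothing about whether they exist. But the point concerns a rule that the article does state. If a serious-event procedure exists, the unqualified sentence conflicts with it; if none exists, the gap is real. The sentence needs a limit in either case.

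**The list names slipping, not fracture or head injury.** Such an injury can be read as unlisted and therefore reportable. This also stands as one reading. It does not help with admission after ingestion, which is on the list, and a safety rule should not depend on which reading a site chooses.

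**The information is already collected, in both arms and often.** This is correct, and collecting expected reactions as trial data is a reasoned choice for licensed products used as in ordinary care. It justifies the exemption for minor events; it does not supply prompt escalation of serious ones.

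**Stronger conclusions do not follow.** A reader might infer any of the following, and the documents support none of them:

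- That serious slips or ingestions need never reach the sponsor. Questionnaire answers feed the trial database.
- That they can be seen only when the trial ends. No section says that the committee is denied safety data, its charter is not shown, and having no interim analyses is not the same as having no safety review.
- That the 20% loss to follow-up (0.20 × 423 = 84.6, about 85 children) counts children whose events go unseen. That figure is a sample-size allowance for the 16-week outcome, and children lost later may have answered earlier forms.
- That serious events are exempted on purpose. The text is unqualified; it does not say so.

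**Conclusion.** The concern holds in limited form. As published, the exemption rests on expectedness with no restriction to non-serious events, and the article states no prompt route from a questionnaire answer about a slip or ingestion to the Trial Steering Committee. The change should be made on safety grounds; it does not affect the validity of the primary analysis.

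The only size that can be put on it is the spacing of forms: 1 week to week 16, then 4 weeks for the remaining 36 of 52 weeks. That describes the schedule, not a count of missed events. The article gives no rate of serious slips or ingestions, so none is estimated. The conclusion assumes that the Monitoring sentences are applied as worded. A serious-event procedure in the full protocol would reduce the practical consequence, but the two texts would then have to be reconciled.

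**What to change.** Add the words *unless serious* to the end of the exemption in the Monitoring section. State that this applies in both arms, and that serious slips, ingestions and skin reactions go to the sponsor and the Trial Steering Committee under the trial's serious-event procedure, using that procedure's definition of serious. If the full protocol already provides for this, a cross-reference is enough.

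Optionally, add a follow-up item asking whether the event needed hospital or emergency care, with positive answers flagged to the trial team when received. The adverse-effect question is the better place for it, because it is on every form, including the weekly ones; the service-use item would overlap with it but is absent from weeks 1 to 15.

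Cost: one sentence, at most one questionnaire item, and probably a handful of extra reports. Sample size and analysis do not change.
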